### 2.7 Statistical analysis plan

Independent t-tests for continuous data and chi-square test (χ2) for categorical data will be conducted to confirm that there were no demographic or clinical differences between groups at baseline. Repeated-measures ANOVAs will be conducted to analyse changes associated with the programs. For the autobiographical memory task and all the biological measures (i.e., genetic measures, EEG, EKG, respiratory rate, and cortisol in saliva), a 2 (Order of program) x 3 (Time) repeated measures ANOVA will be conducted. For the self-report psychological measures, a 2 (Order of program) x 4 (Time) ANOVA will be conducted. We will use age, sex, and previous meditation experience as covariates in the main analyses. Assumptions of normality, homogeneity of variances, sphericity, and homogeneity of covariances will be checked. Further analyses will include post-hoc, p-corrected comparisons (e.g., Bonferroni). All analyses will be performed with SPSS 28.0 (IBM Corp., 2021) or R Studio statistical software (R Core Team, 2021). Two-tailed tests will be used to determine significance at the 5% level.

The EPIC methylation arrays´ raw data will be normalised and filtered by a robust bioinformatics pipeline procedure [69]. We will then perform an unsupervised analysis of the data via hierarchical clustering, i.e., PCA and t-SNE (by R Studio). In parallel, taking advantage of the known DNA methylation signatures related to distinct cell types or molecular processes, we will: 1) characterize the proportion of different immune cells, and 2) determine the epigenetic age with Horvath’s model or other epigenetic clocks to capture the influence of lifestyle on the DNA methylome [70, 71]. This may reveal a link between the MBI programs and the immune response, inflammation, and cells’ physiological condition. Finally, we will focus on supervised analyses to identify differential DNA methylation biomarkers in the two groups (MBRS first *vs* CCT first) and time points: day 1(baseline), day 4 (program switch), and day 7 (post retreat).

The EEG signals will be assessed both at the sensor level and the source’s space. Source space reconstruction would be performed using the eLoretta procedure over the MNI template. The analysis will be conducted two-fold: 1) the power spectral profiles of each condition (eyes closed and eyes open) will be computed using the fast Fourier transform algorithm; 2) the functional networks will be calculated using a phase synchronization algorithm (i.e., phase locking value). The functional networks will be created using standard regions of interest defined over the AAL atlas.

Diurnal Cortisol Slope (DCS) will be calculated individually for each participant as a function of their respective bedtime and awakening times. DCS will be calculated as awakening cortisol subtracted from bedtime cortisol, divided by each subject’s total waking hours.

Intention-to-treat (ITT) analyses will be conducted with all participants, regardless of session or outcome measure completion. The pattern and percentage of missing data will be explored before analysing the data. It should be noted that the chances of missing data will be minimized because the questionnaire administration format via Qualtrics does not allow progress to be made until all items in each questionnaire are completed. Binary logistic regression will be used to evaluate the assumption that data is Missing at Random (MAR). ITT mixed models (restricted maximum likelihood (REML) estimation) will be used to account for missing data MAR. If missing were not random (MNAR), we would conduct Multiple Imputation and Pattern Mixture Models incorporating the predictor responsible for the missingness into the model. In any case, sensitivity analysis will be performed, comparing the main outcomes between completers and imputed values. To safeguard the confidentiality of participants’ data, all samples will be anonymized with alpha-numeric codes. These codes will not carry any personal information. Personal data linked to the alpha-numeric code will not be included in any files used for data analyses and will remain separate from the main database. Data displayed in public repositories (e.g., GitHub or datadryad.org), linked to the resulting publications, will always be anonymized. Data supporting each published study will be included within the article and/or supporting materials. To improve blinding integrity [72], personnel who will analyse the data collected from the study are not aware of the treatment applied to any given group. The authors will be fully responsible for handling and analyzing data independently from any sponsor. All the questionnaires included in the protocol as well as a copy of the informed consent, are available at https://osf.io/gczas/?view_only=7864451a24cf4a82824f6f298b1bbf0f.

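### Section 2.7 does not say whether complete-case repeated-measures ANOVA or the REML mixed model is primary, and covariate coding is left open in a way that could weaken the Time test

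*Protocol article*

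**What the plan says.** All of the following stands in section 2.7 of the protocol article unless noted.

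- **Model.** "Repeated-measures ANOVAs will be conducted to analyse changes associated with the programs". For the autobiographical memory task and the biological measures, "a 2 (Order of program) x 3 (Time) repeated measures ANOVA will be conducted". For the self-report measures, "a 2 (Order of program) x 4 (Time) ANOVA will be conducted".
- **Covariates.** "We will use age, sex, and previous meditation experience as covariates in the main analyses". Nothing is said about centring, the coding of sex, or covariate-by-time terms.
- **Software.** "All analyses will be performed with SPSS 28.0 (IBM Corp., 2021) or R Studio statistical software (R Core Team, 2021").
- **Population.** "Intention-to-treat (ITT) analyses will be conducted with all participants, regardless of session or outcome measure completion".
- **Missing data.** "ITT mixed models (restricted maximum likelihood (REML) estimation) will be used to account for missing data MAR". If data are not missing at random, multiple imputation and pattern mixture models follow. A comparison of completers with imputed values is planned in any case.

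No sentence says that the mixed model replaces the ANOVA, or when. Section 2.1 and Table 2 place biological and task measures on days 1, 4 and 7 only. The 3- and 12-month follow-ups are questionnaires only. Section 2.2 admits adults aged 25 to 65, and section 2.3 plans 52 participants.

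**The concern.** Two models are prescribed for the same repeated outcomes, and they answer to different populations. The ANOVA drops anyone with a missing assessment; the stated population is everyone. An analyst could run either, call it the main analysis, and be within the text. For self-report outcomes, absence at a follow-up would also remove that person's complete retreat data.

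The covariates add a quieter risk. The joint hypotheses at the end of the Introduction concern change under both programs together, so where they are tested by ANOVA the Time effect carries them. SPSS repeated-measures GLM adds covariate-by-time terms by default and does not centre covariates. The omnibus Time test then describes change for someone with covariate values of zero, including age zero. R with additive between-subject covariates does not do this. The two permitted packages could therefore test different hypotheses under the same label.

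**Working it through.** **1. The plan's own sample size.** Section 2.3 asks for 21 per group and adds 20%: 21 x 1.2 = 25.2, rounded up to 26, or 52 in total. That step reproduces. The 21 itself cannot be confirmed, because neither the correlation between assessments nor the metric of the 0.37 effect is given. It is not shown to be wrong, and the point here does not depend on it.

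**2. Who the ANOVA keeps.**
- Biological measures and memory task, three times: days 1, 4 and 7. Only a missed retreat assessment removes a participant.
- Self-report, four times: for the scales given on days 1, 4 and 7 and at follow-up (for example DASS-21), the fourth time must be a follow-up. PHQ-9, PHQ-15 and SWLS have only home screening and day 7 before follow-up, so four times would need both follow-ups. Either way at least one is included; which one is not stated.
- The online forms prevent skipped items, not missed visits.

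Complete cases out of 52, assuming independent loss at each visit (the rates are assumptions):

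| Loss per visit | 3 visits | 4 visits |
|---|---|---|
| 3% | 0.97^3 = 0.913, 47.5 | 0.97^4 = 0.885, 46.0 |
| 5% | 0.95^3 = 0.857, 44.6 | 0.95^4 = 0.815, 42.4 |
| 10% | 0.90^3 = 0.729, 37.9 | 0.90^4 = 0.656, 34.1 |

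To show what such losses cost, take a linear change of 0.5 SD over three times, correlation 0.5 and centred covariates (all assumed). Simulated power of the Time test is 0.90 with 52 completers, 0.81 with 42 and 0.75 with 36. A mixed model keeps the retreat data of someone who misses only a follow-up.

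**3. Time test with uncentred age, SPSS-style.** For age alone, the standard error at age zero relative to mean age is sqrt(1 + mean^2/variance).
- Ages uniform 25 to 65 (assumed): mean 45, variance 40^2/12 = 133.3, so sqrt(1 + 2025/133.3) = 4.02.
- Mean 45, SD 8 (assumed): sqrt(1 + 2025/64) = 5.71.

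For the omnibus test the noncentrality is n_eff x f^2 x m/(1 - rho), where n_eff is the effective sample size for Time. With centred covariates n_eff is 52. With raw age and raw experience (assumed exponential, mean 5 years) and effect-coded sex, it is about 1.4 (age SD 8) to 2.8 (uniform ages). With m = 3 and rho = 0.5 (assumed):

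| Reading of 0.37 | Multiplier f^2 x 3/0.5 | Centred: noncentrality, power | Raw: noncentrality, power |
|---|---|---|---|
| f = 0.37 | 0.821 | 42.7, about 1.00 | 1.15 to 2.30, 0.14 to 0.25 |
| d = 0.37, so f = 0.185 | 0.205 | 10.7, 0.83 | 0.29 to 0.57, 0.07 to 0.09 |

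A simulation of the day 7 minus day 1 change (4,000 runs, N = 52, uniform ages, covariates unrelated to change, standardised change 0.52) gave power of 0.95 without covariates, 0.95 centred and 0.13 raw.

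**4. What coding does not touch.** Regress a within-subject contrast on an intercept, sequence and covariates. Shifting a covariate by a constant alters only the intercept, so the sequence coefficient, which is Order x Time, is unchanged. Simulated Type I error with raw covariates was 0.052.

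**The case against.** The plan does address missing data. It names mixed models, multiple imputation, pattern mixture models and a completer comparison, and the mixed model can be read as the method for use once data are missing. A reader who concludes that the plan simply discards incomplete cases goes too far. What stands is narrower: the text never says which model is primary.

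A reader might also infer that loss at 12 months cuts every contrast, for example to between 42 and 31 of 52 at 20% to 40% loss. The documents do not support that. Biological and task outcomes end on day 7, the fourth self-report time may be 3 months, and the loss rates are not in the documents. At 20% loss, 42 remain, which is the 21 per group that section 2.3 asks for.

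The third tempting inference is that power is destroyed for hypotheses a to f. That would need SPSS, its default interaction terms and uncentred covariates together. The article allows R and is silent on centring, a detail that a condensed article may leave to a fuller plan. Even in SPSS, comparisons of estimated marginal means are made at the covariate means. Methylation has separate supervised analyses, and the Arithmetic Stress Test is not explicitly assigned to a model. The sequence question rests on Order x Time, which is unaffected. All of this stands, so the age-zero problem is a hazard to close, not an error that the plan states.

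**Conclusion.** The conflict between the ANOVA and the all-participants principle is in the text and unresolved. Its effect is largest for self-report outcomes, where a missed follow-up removes good retreat data: at 3% to 10% assumed loss per visit, about 46 to 34 of 52 participants are complete over four visits. For the three-level outcomes the range is about 47 to 38, and only missed retreat assessments count.

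The covariate hazard is conditional on package and coding. If it occurs, the standard error for Time rises about fourfold with uniform ages, and more if ages cluster, and the omnibus Time test loses most of its power. It costs power, not Type I error. The sizes rest on assumed age and experience distributions, a correlation of 0.5 and an unstated effect metric; the direction does not depend on the exact values. The point should be corrected before analysis; it does not undermine the design.

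**What to change.** In section 2.7:

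- Name the REML mixed model already in the plan as the single main analysis for the repeated outcomes now assigned to ANOVA, with all randomised participants and all available assessments.
- Keep repeated-measures ANOVA as a sensitivity analysis in completers.
- State that age and meditation experience are mean-centred and sex is effect-coded in both models. The Time test then refers to an average participant in either package.

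The cost is a few sentences. No data, visits or participants are added, and the model is already planned.

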As, to the best of our knowledge, this is the first study using a sequential design with two intensive meditation modalities, it is difficult to formulate specific hypotheses regarding the separate and combined effects of the MBSR and CCT programs on the selected outcomes. Thus, considering the two MBIs jointly, we expect that both programs will significantly: a) modify the DNA methylation and expression levels of specific genes and a reduction of the DNA methylation-based biological clock; b) reduce participants’ levels of psychological distress while increasing their levels of psychological functioning (i.e., mindfulness, compassion, emotion regulation, and well-being); c) change the EEG spectral profile of the resting state brain activity (i.e., changes in the balance between Alpha (8–14 Hz) and Theta (4–8 Hz) frequency bands and, regarding the organization of the brain functional networks, a modulation of the difference between the activation of the default mode network and the one corresponding to the salience network); d) alter awakening and bedtime cortisol levels leading to a steeper Diurnal Cortisol Slope (DCS); e) improve the efficacy of mood regulation following a negative mood induction (using an autobiographical memory task); f) reduce participants’ reactivity in an objective experimental stress test (i.e., Arithmetic Stress Test). In addition, given the multidisciplinary nature of the present project, we intend to provide a comprehensive view of potential changes in various areas of biological and psychological functioning and their interrelationships.

In general, we expect an overall pattern of results in which changes will be significantly higher for the combined effects of both MBIs than for each program separately. Moreover, based on previous literature comparing standard MBSR and CCT programs [24], we expect no major differences in primary outcomes between both programs, although the mechanisms of change may be different; in general, changes in MBSR will be mediated by cognitive variables (e.g., mindfulness) whereas changes in CCT will be mediated by socio-emotional variables (e.g., compassion). We also expect that the self-reported psychological changes associated with the MBIs will remain 3 months after the programs.

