The screening procedure will be conducted as follows: 1) First contact will be made through an online form expressing interest and commitment to participating in the study, where participants will be provided with some information on the retreat (date, location, and program characteristics) and will complete information on demographics, physical and psychological health history, and meditation experience. A waiting list will be formed for participants who did not sign up in time and wished to be considered in case a place became available. An expected final sample of 52 people will take part in the retreat being randomised to the MBSR training or CCT training for the first part of the retreat. All participants will complete the first arm of the study and then, after a half-day break, will be allocated to the opposite condition for the second study arm (following a cross-over design). There will not be a longer wash-out period due to the difficulties of extending the participants’ stay in the retreat for more days. However, in psychological studies with a cross-over design (e.g., [40]) there are usually no long periods between treatments. Moreover, introducing a wash-out period (days, weeks, or months) would introduce difficult-to-control confounders (e.g., different life events experienced by individuals) and would make comparability of treatments more difficult.

Participants will pay the cost of the retreat (i.e., meals and accommodation only) and will not receive any economic compensation for their contribution to the study. Participation requires informed consent, provided by the principal investigator (PI) or authorized full members of the research team, in which all the conditions of the study are reported. In case of any adverse effect, which is very unlikely in this type of intervention, participants may leave the study at any time without having to offer any explanation and without any kind of penalty. Furthermore, the team will facilitate any kind of help requested by participants during the retreat. The collection of biological information is innocuous, and blood and saliva samples will be collected by nursing professionals. Participants will be allowed to drop out at any point during the study as stated in the informed consent.

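### The Order x Time interaction mixes the Day-4 program difference with the Day-7 order difference, so it cannot answer the two stated aims separately; two baseline-adjusted contrasts would.

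*Protocol article*

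**What the plan says.** The Introduction (section 1) gives two comparative aims: whether MBSR and CCT produce different changes, and whether their sequence affects the results. Section 2.1 places the Day-4 assessment after the first program and before the second, and the Day-7 assessment at the end. Section 2.2 allows a half-day break between programs and adds: "There will not be a longer wash-out period".

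For the memory task and all biological measures, section 2.7 states that "a 2 (Order of program) x 3 (Time) repeated measures ANOVA will be conducted". For the self-report measures, "a 2 (Order of program) x 4 (Time) ANOVA will be conducted". On adjustment: "We will use age, sex, and previous meditation experience as covariates in the main analyses". The outcome's own Day-1 value is not on that list; it enters only as the first level of Time. Follow-up testing is described as "Further analyses will include post-hoc, p-corrected comparisons (e.g., Bonferroni"), with no time point or contrast named. A supervised methylation analysis is to "identify differential DNA methylation biomarkers in the two groups" and across Days 1, 4 and 7, again without a stated contrast or baseline adjustment. Baseline t-tests and chi-square tests are planned "to confirm that there were no demographic or clinical differences between groups at baseline".

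**The concern.** The two aims correspond to two different group comparisons. At Day 4, MBSR-first minus CCT-first is a randomised comparison of one program with the other, made before anyone starts the second program. At Day 7 everyone has had both, so the same subtraction measures the effect of order, including any carry-over. With only half a day between programs, the second period cannot supply a clean program comparison.

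The planned interaction asks only whether the group difference varies in any way over time. It rejects for a program difference at Day 4, for an order difference at Day 7, or for any mixture, and does not say which. In the 2 x 4 model the follow-up level is mixed in as well. A significant interaction could therefore be reported as evidence on either aim when it identifies neither.

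The second issue is efficiency. With Day 1 as a level of Time, the Day-4 group contrast of changes in this model is a comparison of change scores. Using Day 1 as a covariate gives a smaller variance in a randomised comparison.

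**Working it through.** **Inputs.** From the article: 26 per group, two-sided alpha .05, two groups, Days 1, 4 and 7, effect size .37 (sections 2.3 and 2.7). The metric of .37 is not stated, so two Day-4 differences are used: .37 SD (read as a standardised mean difference) and .74 SD (read as Cohen's f for two groups, 2 x .37). Assumed, because the article gives neither: a common correlation rho between occasions, shown from .3 to .9, and compound symmetry.

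**The plan's own figure.** The inflation step reproduces: 21 x 1.2 = 25.2, rounded up to 26. The 21 per group cannot be verified without the unstated correlation. It is not a calculation for a Day-4 contrast and is not needed below.

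**Step 1: what the interaction responds to.** With group differences D_j over three occasions and n per group, its noncentrality is

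lambda = (n/2) x sum(D_j − mean D)² / (1 − rho), on 2 and 100 df.

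- Day 4 only (0, d, 0): the sum is d²(1/9 + 4/9 + 1/9) = (2/3)d².
- Day 7 only (0, 0, d): the same, (2/3)d².
- Both days (0, d, d): d²(4/9 + 1/9 + 1/9) = (2/3)d².

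The three noncentralities are identical for every rho. At d = .74 and rho = .5: 13 x .5476 x .6667 / .5 = 9.49, power .78. At d = .37 power is .255, again for all three patterns.

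**Step 2: variance of the Day-4 contrast.** In SD² units, the change score has variance 2(1 − rho) and the baseline-adjusted contrast (ANCOVA) 1 − rho². The ratio is 2/(1 + rho).

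| rho | .3 | .5 | .7 | .8 | .9 |
|---|---|---|---|---|---|
| change / ANCOVA variance | 1.54 | 1.33 | 1.18 | 1.11 | 1.05 |

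**Step 3: power for a difference at Day 4 only.** ANCOVA: lambda = (n/2)d²/(1 − rho²), on 1 and 49 df. At d = .74 and rho = .5: 13 x .5476 / .75 = 9.49. This equals the interaction's lambda, but it is spent on 1 df instead of 2, hence .86 against .78.

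| rho | d = .74: ANCOVA | d = .74: 2x3 interaction | d = .37: ANCOVA | d = .37: 2x3 interaction |
|---|---|---|---|---|
| .3 | .78 | .63 | .28 | .19 |
| .5 | .86 | .78 | .33 | .26 |
| .7 | .96 | .95 | .45 | .40 |
| .8 | .99 | .99 | .59 | .57 |
| .9 | 1.00 | 1.00 | .85 | .87 |

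Above rho = .5 the interaction has the larger noncentrality for this pattern, because Day 7, with no difference, acts as a second reference occasion. The power advantage of the single contrast then shrinks, and at rho = .9 with d = .37 it reverses slightly.

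**The case against.** **Day 4 may be reached anyway.** Group comparisons at each time point are the usual follow-up to an interaction, the methylation analysis names Day 4, and the REML mixed models in section 2.7 could yield a Day-4 contrast. This stands: a reader might infer that the plan never looks at Day 4, and the article does not support that. What remains is that the contrast is not named in advance or stated to be baseline-adjusted. If the follow-up were an unadjusted Day-4 difference, Bonferroni-corrected over three occasions (an assumption), power at .74 SD and rho .5 would be .58, against .725 for the baseline-adjusted contrast under the same correction.

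**Contrast-level detail belongs in a full analysis plan.** This stands for similarity margins, a primary outcome for the contrast and a multiplicity scheme; none of these is claimed as missing. But the article positively fixes the model and the covariate list, and the point concerns that choice.

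**The precision loss depends on an unstated correlation.** This stands, and the range is shown. Day 1 to Day 4 is short, so high correlations are plausible for some outcomes, and there the gain over the interaction vanishes.

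**Stronger readings.** A reader might judge the plan by the Order main effect, which has power of only .19 for a .74 SD difference at Day 4 alone (rho .5). Nothing in section 2.7 assigns the program question to that test. A reader might also infer from "we expect no major differences in primary outcomes between both programs" that a non-significant result will be reported as similarity. The article states an expectation there, not a decision rule.

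**Conclusion.** The point holds as one about separating the two aims. The planned interaction cannot distinguish a program difference at Day 4 from an order difference at Day 7; under compound symmetry the equality of the three noncentralities does not depend on rho. Precision is secondary: a Day-4 change-score contrast has 5% to 54% more variance than the baseline-adjusted one for rho .9 down to .3. Against the interaction itself, there is a clear power gain at low to moderate correlation and none at high correlation. All power figures rest on the assumed correlations, compound symmetry and a difference at Day 4 only.

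Hypotheses (a) to (f), framed for the two programs jointly, rest on the Time effect and are not affected. Nor can .37 SD serve as a fixed yardstick for the precision of the contrast, since the article does not say whether .37 is an f or a standardised mean difference.

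**What to change.** For every outcome measured on Days 1, 4 and 7, pre-specify one model adjusted for the participant's Day-1 value, sex (the randomisation stratum), age and meditation experience, and take two 1-df contrasts from it:

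1. Day 4, MBSR-first minus CCT-first: the program effect.
2. Day 7, the same difference: the order effect, including carry-over.

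Report each with a 95% confidence interval. By Table 2, PHQ-9, PHQ-15 and SWLS have no Day-4 value, so contrast 1 is not available for them; the plan should say so. The Time effect can stay for the joint hypotheses. Describe baseline characteristics by group instead of testing them, since a non-significant test cannot confirm the absence of differences.

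The cost is a change of wording in the analysis plan and one degree of freedom per model. No new data are needed.

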***b*.*2) Emotion regulation*.** A 10-min retrieval of autobiographical negative memories. Participants will receive a link through Qualtrics for a baseline assessment (three days before the retreat) where they are asked to think about three negative autobiographical memories of events for which they felt responsible and made them feel negative emotions such as shame, guilt, and sadness. Participants will be asked to assign personal keywords (e.g., ‘traffic accident’), for each of the three memories, synthesizing the event. Each of the three negative events will be randomly assigned to the three respective assessment days so that participants were given the corresponding “keywords” when they begin the retrieval task. Participants are given 10 minutes to write down the memory as specifically as possible. Pre-post changes in their sadness, happiness, anxiety, serenity, shame, and guilt affect states will be assessed using a 0 (nothing) to 100 (very much) visual analog scale. These two laboratory psychological tasks will be completed by each individual while alone in a quiet room, using a portable computer.

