#### 2.5.4 Salivary sampling and cortisol measurement

Participants will be given Salivette® cortisol saliva sample collection tubes (Sarstedt, Germany) that contain a sterile cotton swab for sample absorption along with detailed verbal and written instructions concerning sample collection. Diurnal Cortisol Slope and cortisol levels at bedtime and awakening will be measured at three different time points of the retreat (see Fig 1). Then, the saliva samples will be stored in the refrigerator until they are delivered to the laboratory after a few hours. Once in the laboratory, the samples will be centrifuged at 3000 rpm for 5 min, resulting in around 1.5–2.0 ml clear supernatant of low viscosity that will be stored at −80°C until the analyses of the salivary cortisol levels. Cortisol, the principal stress glucocorticoid produced by the hypothalamic-pituitary-adrenal axis (HPA) [68], will be assessed using a commercially available enzyme-linked immunosorbent assay (Salimetrics®) having an approximate sensitivity of <0.007 μg/dL.

Table 2 shows a description of all measures and time points.

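### No primary outcome is designated, and each outcome's ANOVA is tested at 5% with correction stated only for post-hoc comparisons

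*Protocol article*

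**What the plan says.** Section 1 lists six expectations, a to f, without ranking them. They cover methylation, expression and the epigenetic clock; distress and functioning; resting EEG; cortisol; mood regulation; and stress reactivity. The section then adds: "we expect no major differences in primary outcomes between both programs". Section 2.7 plans a sensitivity analysis "comparing the main outcomes between completers and imputed values". Neither term is defined. Section 2.5 and Table 2 group the measures by domain and give none priority. Section 2.3 takes its effect size from well-being results in earlier retreats but does not call well-being primary.

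The testing rule is explicit. For the memory task and the biological measures, "a 2 (Order of program) x 3 (Time) repeated measures ANOVA will be conducted". The questionnaires have a parallel rule with one more time point: "For the self-report psychological measures, a 2 (Order of program) x 4 (Time) ANOVA will be conducted". The threshold is given once for everything: "Two-tailed tests will be used to determine significance at the 5% level". The only correction mentioned is this: "Further analyses will include post-hoc, p-corrected comparisons (e.g., Bonferroni". No ordering of hypotheses, division of alpha or false-discovery control across outcomes is stated.

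**The concern.** A hypothesis about primary outcomes cannot be judged if no outcome is primary. The same holds for a sensitivity analysis on main outcomes. Under the stated rule, every omnibus test of every measure stands alone at 5%, and the correction begins only at the follow-up comparisons. Six domains, each expected to change significantly, are then read from a long list of tests with no limit on the overall chance of error.

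The order of the two programs is a headline question in sections 1 and 3, and it is answered by the Order x Time tests. The article itself expects little difference between programs on its primary outcomes. One or more chance interactions among about 20 could therefore be read as an order effect, and nothing in the plan says which outcome decides the matter.

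**Working it through.** **The plan's own figures.** The article states no family-wise error rate. Its only alpha is 0.05, undivided, in sections 2.3 and 2.7. The 21 per group can be reached with the between-group test of a repeated-measures ANOVA, with noncentrality N·m·f² / (1 + (m − 1)ρ). For N = 42, m = 5, f = 0.37 and ρ = 0.26 this is 28.75 / 2.04 = 14.1, and power is 95.6%. At ρ = 0.27 power is 95.2%. The article gives neither ρ nor the effect tested, so the figure cannot be confirmed or called wrong. It is the power of a single test at 5%.

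**Number of outcomes.** Section 2.5.4 says "Table 2 shows a description of all measures and time points". The table has 3 epigenetic, 11 self-report, 4 task, 3 psychophysiological and 1 cortisol row: 22. Dropping the Perceived Stress Scale (screening only) and the adverse-effects scale leaves 20. PANAS and STAI are the responses to the arithmetic task, so merging those three rows into one gives 18. In the other direction, section 2.5.4 describes three cortisol measures (slope, bedtime, awakening), and the memory task has six ratings: "Pre-post changes in their sadness, happiness, anxiety, serenity, shame, and guilt affect states will be assessed". Counting those gives 18 + 2 + 5 = 25.

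**One test per outcome, all nulls true, independent outcomes.** The chance of at least one false positive is 1 − 0.95^K.
- K = 18: 60%
- K = 20: 64%
- K = 25: 72%

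The expected number at K = 20 is 20 × 0.05 = 1.0, whatever the correlation.

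**Correlated outcomes and more than one effect per ANOVA.** The article gives no correlation between outcomes, so 0 to 0.7 is assumed. The second column below simulates 20 equally correlated two-sided tests. The last two simulate twenty 2 x 3 ANOVAs with 26 per group and no true effects. The self-report measures are planned as 2 x 4, but each null test there also has size 5%.

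| Correlation | One test per outcome | Time or Order x Time | Order, Time or interaction |
|---|---|---|---|
| 0 | 64% | 87% | 96% |
| 0.3 | 54% | 79% | 90% |
| 0.5 | 42% | 68% | 82% |
| 0.7 | 29% | 50% | 66% |

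With one test per outcome the chance passes below 50% at a correlation of about 0.37.

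**Price of correcting across all 20.** Bonferroni would require 0.05 / 20 = 0.0025 per test. In the between-group model above with ρ assumed to be 0.25, power at 42 participants falls from 96% to 71%. At 52 it is 84%, and about 70 participants are needed for 95%. One named primary test at 5% needs no change to the sample size on account of multiplicity.

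**The case against.** The strongest reply is that this is a condensed article. A separate analysis plan may deal with multiplicity among secondary outcomes, and the registry record, which was not available for this review, may name a primary outcome. That stands as a limit: a reader should not infer that the trial has no primary outcome anywhere. It does not remove the point, because the article uses the terms in a hypothesis and in a planned analysis, and its own section 2.7 states the 5% rule and where correction applies.

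The second reply is that the probabilities require every null hypothesis to be true, while section 1 cites evidence that such programs work. This also stands. A reader might infer that a false positive is more likely than not in this trial. The document does not support that without the all-null condition and, on one test per outcome, a correlation below about 0.37. The condition is most plausible for Order x Time, given the article's own expectation of no major program differences.

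Third, the study is partly framed as exploratory, and whether separate domains need one shared error rate is debated. Yet the article expects significant change in six domains. The stronger inference, that any significant result could be presented as confirming any hypothesis, does fail: each expectation is tied to its own domain, so a cortisol result cannot confirm the self-report expectation.

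Other tempting overstatements:
- EKG and respiration are measured but belong to none of the six expectations.
- Not all six expectations are directional: the EEG one, and part of the epigenetic one, predict only change.
- Well-being is not wholly absent on Day 4. Table 2 omits the Satisfaction with Life Scale that day, but the daily scale in section 2.5.2 has a well-being item.
- An array-level correction may be part of the cited methylation pipeline. The article does not say so, and it would not cover the other domains.

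**Conclusion.** The point holds. Primary and main outcomes are invoked but not designated, and the stated rule does not control error across six expectations or about 20 outcomes. Under the global null, the chance of at least one false positive is 64% with one test per outcome and independence, 54% at a correlation of 0.3 and 42% at 0.5. Counting Time and Order x Time, it is about 87%, 79% and 68%. These figures rest on the count of 20 rows, equal correlation between outcomes (assumed, not documented) and no true effects. They show what the rule permits and do not predict this trial's results. The sample size itself is not disputed here.

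**What to change.** In section 2.7:

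- Name one primary outcome measured on Days 1, 4 and 7. DASS-21 qualifies; the Satisfaction with Life Scale does not, as it is not scheduled on Day 4.
- Name one primary contrast, tested at 5%, that matches the hypothesis the trial means to confirm. A Day 4 comparison between groups need not be the choice: section 1 expects no major program difference in primary outcomes, and its main predictions concern the programs jointly.
- Name one lead measure for each of expectations a to f and apply Holm across the six, with a smallest threshold of 0.05 / 6 = 0.0083. For expectation a this means fixing the measure, including which epigenetic clock if a clock is chosen, since section 2.7 leaves that open.
- Label all other outcomes exploratory, including EKG and respiration, with false-discovery-rate control within domain.
- Replace the undefined references in sections 1 and 2.7 with the named outcome, and align them with the registry record.

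In section 2.3, state that the power applies only to the named primary test. If that outcome is not a well-being measure, the effect size needs its own justification.

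The cost is protocol or analysis-plan text plus a registry and Ethics Committee notification, made before analysis, and somewhat lower power for the secondary domains. Holm's strictest step of 0.0083 is milder than the 0.0025 that Bonferroni over 20 outcomes would need. No data collection changes.
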